### Randomization

Randomization will take place at the ranch level prior to recruitment of participants into the study. Two ranches matched on location, type of berry, size (whenever feasible) will be randomized with the 1:1 ratio sequentially when the two ranches are available for participation, using a uniform distribution for random number generation. At least six ranches will be randomized to intervention or control. We will recruit approximately 100 workers at each ranch. In total, the study will recruit up to 600 workers. Due to the nature of the intervention and because the intervention takes place at the ranch, the participants as well as the research assistants collecting data will not be blinded.

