### Incentives

Subjects will be given a $25 gift card at the baseline, post-intervention, and 6-month data collection points and a $50 gift card at the 1 and 1.5-year data collection point. Participants may be given a water bottle and/or bandana (or other similarly valued items) at the end of the educational sessions or at supplemental activities. All control participants in matched ranches will complete follow-up data collection at approximately the same time as their intervention work crew.

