### Power calculation and sample size

For a CRT, we computed sample size (N) assuming independence (i.e., simple random sampling) suited for standard randomized control trial (RCT) that randomizes individuals to interventions, and then multiplied the resulting sample size estimate by the inflation factor (IF). Here, IF is defined as IF = [1 + (m-1)*ρ], where m is the average cluster size and ρ is the intra-class correlation (ICC). For the N calculation under simple random sampling, we used the estimates reported from Ackerman et al. [26]. In this study, the intervention group achieved 6% weight loss and control group achieved 2% weight loss, at 4–6 and 12–14 months of follow-up with standard deviation (SD) approximately 4.4% in both groups, where percent weight loss was the primary outcome [26]. In our calculations, we used somewhat conservative estimates: mean difference of 4 and 3% with SD of 5%. To achieve 80% power with alpha level of 5% using two-sided, two-sample t-test, the minimal total N required for detecting 4% difference is 52 (26 per group) and that for detecting 3% difference is 90 (45 per group). Noting that the average cluster (ranch) size in our study is 100, Table 2 provides estimates of total N and the number of clusters needed for different values of ICC and mean difference in the outcome. Based on these calculations, we believe a total of 4–6 clusters may be justifiable. However, we understand the possibility of confounding between intervention effect and cluster effects (i.e. ranch in this study), and these potential limitations in generalizability will be accounted for in data analyses and acknowledged in interpreting the results.

**Table 2 Tab2:** Power/Sample size calculations

Mean difference (SD = 5%)	ICC	IF	Total N needed for individual randomization	Total N needed for CRT	Total # of clusters = N/100^a^
4%	0.01	2.99	52	156	2
	0.02	4.98	52	259	4
	0.05	10.95	52	570	6
3%	0.01	2.99	90	270	4
	0.02	4.98	90	449	6
	0.05	10.95	90	986	10

^a^Rounded up to even number integer

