### Statistical analysis plan

Analyses will use a modified intent-to-treat basis to assess the effects of the intervention regardless of adherence [37, 38]. Data collected for the primary outcome will be analyzed and summarized by standard descriptive statistics. We will analyze continuous outcomes (body weight and BMI change from baseline to end of follow-up and between intervention and control) using the mixed effects model accounting for ranch as a cluster variable. Control of other important covariates such as gender, baseline weight/BMI may be made in sensitivity analyses. Analysis of secondary outcomes will be conducted in a similar fashion. In these analyses, we will estimate ICC and report them along with other design characteristics including cluster size and number of clusters. We will not adjust for multiple testing in the analysis of the primary outcome (weight and BMI, which are virtually a single outcome as height does not change), but clearly report the analyses of secondary outcomes as secondary in publication. No interim analyses will be conducted.

Data collected to address economic evaluation, including intervention costs, health outcomes and medical costs, and worker productivity will be combined with accounting data to assess the overall economic cost/gain of the intervention. Accounting data will be compared to costs produced by the UCD Department of Agricultural and Resource Economics, which does not include costs of obesity program interventions, but does provide guidance on related issues. For example, a ranch benefits economically if a worker’s harvesting rate improves because overall harvest cost falls when worker productivity improves. Moreover, absenteeism adds uncertainty and cost of maintaining a larger workforce for equivalent production.

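### The stated primary model accounts for ranch only, although ranches are randomised in matched pairs, and fixes no small-sample reference for about six ranches

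*Protocol article*

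**What the plan says.** The Randomization section sets the design: "Two ranches matched on location, type of berry, size (whenever feasible) will be randomized with the 1:1 ratio sequentially". It plans at least six ranches with about 100 workers each, hence about three pairs. The Incentives section ties the timing of assessment to the pair: "All control participants in matched ranches will complete follow-up data collection at approximately the same time as their intervention work crew". Under Study design, recruitment is staggered across ranches. Members of a pair therefore share crop, location and calendar time by design, while different pairs may differ on all three.

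The Statistical analysis plan section describes one primary model, a comparison of change between arms "using the mixed effects model accounting for ranch as a cluster variable". Covariates enter only in possible sensitivity analyses; the examples given are gender and baseline weight or BMI. Neither the pair nor the matching factors are mentioned. No reference distribution or degrees-of-freedom method is named, small-sample or large-sample. The section does commit to reporting the ICC, cluster size and number of clusters.

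The Power calculation section starts from an individual-level test, "To achieve 80% power with alpha level of 5% using two-sided, two-sample t-test", and multiplies the result by an inflation factor. It acknowledges possible confounding of the intervention with ranch and says that this will be dealt with in the analysis, without saying how.

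**The concern.** The unit randomised is a ranch within a matched pair, so the stated model does not follow the randomised structure. With three ranches per arm, the between-ranch variance is estimated on 4 degrees of freedom. The choice of reference then moves the two-sided 5% critical value from 1.96 (z) to 2.78 (t on 4 df) or 4.30 (t on 2 df, three pair differences). The same data could be significant under one choice and clearly not under another.

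The two gaps pull in opposite directions. A large-sample reference makes intervals too narrow. Leaving out an effective pair puts between-pair variance into the standard error and makes intervals too wide. Which one prevails depends on a choice that the article leaves open and on how well the matching worked.

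The sample size gives no sign that ranch-level degrees of freedom were considered. Table 2 accepts 2 clusters in its first row (4% difference, ICC 0.01), and an unpaired ranch-level test on two ranches has 2 − 2 = 0 degrees of freedom.

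**Working it through.** **Inputs from the article.** Two-sided 5% test and 80% power; "mean difference of 4 and 3% with SD of 5"%; ICC 0.01, 0.02 and 0.05 (Table 2); 100 workers per ranch; six ranches, so k = 3 per arm. **Assumed, not in the article:** equal ranch sizes, and the share of between-ranch variance common to a pair, varied from 0 to 90%.

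**The plan's own figure.** An exact two-sample t calculation gives 26 and 45 per group, hence totals of 52 and 90, as stated. (The printed inflation factors follow from a cluster size of 200, not 100. That is a separate matter and is not used here.)

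**Step 1: power at ranch level.** SE = 5·√(2·[1 + 99·ICC]/(3·100)). At ICC 0.05, SE = 5·√(2 × 5.95/300) = 0.996, so a 3% difference gives a noncentrality of 3/0.996 = 3.01. Power for six ranches of 100:

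| Difference | ICC | z | t(4) | t(2), no gain from matching |
|---|---|---|---|---|
| 4% | 0.01 | 1.00 | 1.00 | 0.91 |
| 4% | 0.02 | 1.00 | 0.98 | 0.80 |
| 4% | 0.05 | 0.98 | 0.85 | 0.57 |
| 3% | 0.01 | 1.00 | 0.97 | 0.75 |
| 3% | 0.02 | 0.99 | 0.88 | 0.61 |
| 3% | 0.05 | 0.85 | 0.62 | 0.39 |

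**Step 2: false-positive rate.** 200,000 null trials per setting, with a ranch random intercept fitted by closed-form REML and the variance truncated at zero. Rates are for ICC 0.01 / 0.02 / 0.05:

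| Pair share | Ranch-only REML, z | Ranch-mean t(4) | Pair-difference t(2) |
|---|---|---|---|
| 0% | 8.4 / 10.3 / 11.7% | about 5% | about 5% |
| 50% | 5.3 / 5.8 / 6.2% | 3.4 / 2.9 / 2.5% | about 5% |
| 90% | 2.8 / 2.3 / 1.8% | 2.3 / 1.6 / 0.9% | about 5% |

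The same REML model read against t(4) rejects 2.0 / 3.3 / 4.5% at a 0% share and less as the share rises.

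**Step 3: does pairing pay?** Power for 3% at ICC 0.05:

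| Pair share | Unpaired t(4) | Paired t(2) |
|---|---|---|
| 0% | 62% | 39% |
| 30% | 64% | 47% |
| 70% | 66% | 68% |
| 90% | 68% | 85% |

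With three pairs, pairing gains only if it removes most of the between-ranch variance; the break-even is near 70%.

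**Step 4: letting the data choose.** Take an idealised rule: 2 df with a pair effect if its estimated variance is positive, otherwise 4 df without one. It rejects about 7.2% at a 0% share, about 6% at 50% and 5.3 to 5.9% at 90%. When matching does nothing, the pair variance is still estimated as positive in half of the trials.

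**The case against.** A reader might infer that the primary intervals are wrong, or that the primary p-value cannot be a 5% test whichever way it is computed. The article does not support either reading. It names no Wald z, and a ranch mixed model can be run with Kenward–Roger, Satterthwaite or ranch-level degrees of freedom. That choice may stand in a fuller plan that is not shown. Even with z, the rate is close to nominal when pairs share about half of the between-ranch variance, and a ranch-mean t(4) is exact when matching is uninformative. The 8 to 12% is therefore a property of one possible reading, not of the documented plan.

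It is also true that ignoring an effective pair inflates no false-positive rate under t(4). It costs power only. With three pairs, an unmatched analysis is a recognised trade-off, because full pairing leaves 2 df. Nor can strong matching be presumed: size is matched only where feasible, and the whole study is in one area (Oxnard). So a pair term in the primary model is not automatically an improvement.

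What remains is narrower. The article does fix a model and its clustering term, and that term leaves out the unit within which allocation was made. The general promise in the Power calculation section to account for ranch effects names no method, and the sample size shows no allowance for few ranches.

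**Conclusion.** The point holds in conditional form. The firm part is that the stated model omits the matched pair, in the primary analysis and in the named sensitivity covariates alike. The conditional part is the error rate: about 8 to 12% if a large-sample z is used and matching is uninformative, falling to 2 to 3% at a 90% pair share; with t on 4 df, at most 5% and conservative when matching is effective.

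These figures rest on six equal ranches of 100, the ICCs of Table 2 and an assumed pair share. More ranches would soften the problem; fewer analysed ranches would worsen it. The matter should be settled before analysis. The article reports follow-up as still in progress, so at that stage it could be fixed in advance.

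**What to change.** In the Statistical analysis plan section:

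1. State that the arm effect in the ranch mixed model is tested with ranch-level small-sample degrees of freedom: t on (ranches − 2), or Kenward–Roger or Satterthwaite where these give the equivalent. Rule out a Wald z.
2. Pre-specify a matched-pair analysis as a sensitivity analysis: a t-test on the within-pair differences of ranch means, on (pairs − 1) df.
3. State that the choice between paired and unpaired analysis will not be made from the estimated pair variance, because the idealised version of that rule exceeds 5% (Step 4).
4. Restate the power on the same ranch-level basis.

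**Cost.** Wording and one additional analysis; no new data. Intervals become wider: the critical value is 2.78 instead of 1.96 for the primary test, and 4.30 for the paired analysis with three pairs. The power to be reported is lower, for example about 62% instead of 85% for a 3% difference at ICC 0.05.

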### Preliminary data from pilot study

In 2010, University of California, Davis (UCD) collaborated with Reiter Affiliated Companies (RAC), the largest fresh multi-berry producer in the world, growing Driscoll’s proprietary varieties of strawberries, raspberries, blueberries, and blackberries year round in the US, and other international locations, on a pilot study [23]. In this randomized controlled study, 254 participants were allocated to either the control or intervention group in a 1:2 ratio for control:intervention. Farmworkers employed by RAC participated in a 10-week diabetes and obesity prevention program developed by UC Davis and delivered in Spanish by *promotores*. The majority of participants were born in Mexico and identified Spanish as their native language. Primary outcomes included change in weight, body mass index (BMI), waist circumference, and fasting blood glucose concentration. Secondary outcomes assessed changes in diet and physical activity. The pilot found small but significant reductions in weight, BMI and waist circumference in participants completing the program; the decreases were statistically significant in women, but not in men. Improvement in knowledge of healthy eating such as the number of recommended servings of fruits and vegetables, how much water to drink and how much to exercise per day was also seen. Self-reported behaviors related to a healthy lifestyle also changed in the positive direction. Participants who completed the program reported increased physical activity as well as changing their eating habits, such as eating more fruit and less fast food, drinking more water and fewer sweetened drinks. Participant retention was high, with 70% overall remaining in the study from baseline to post-intervention [23]. After the successful completion of the pilot study, we aim to implement and evaluate the effectiveness of the program on a larger scale by recruiting more participants and with a longer follow-up period. The central hypotheses of this project are that a lifestyle intervention delivered at the agricultural worksite will reduce obesity and diabetes risk for employees and will prove to be cost effective for the employer.

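### Adjustment for gender and baseline weight/BMI is optional and kept out of the primary model, although about three ranches per arm cannot be relied on to balance worker mix

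*Protocol article*

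**What the plan says.** The Statistical analysis plan section describes a mixed effects model for change in body weight and BMI, with ranch as the cluster variable. It names no other term beyond the comparison of arms. On covariates it says: "Control of other important covariates such as gender, baseline weight/BMI may be made in sensitivity analyses". Secondary outcomes are to be handled in a similar way.

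Other sections bear on this choice:

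- Randomization: "At least six ranches will be randomized to intervention or control", at 1:1, so about three per arm at the minimum. Pairs are matched on location, berry type and, where feasible, size. Gender mix and baseline weight are not matching factors. Ranches are allocated before workers are recruited, and participants and data collectors are not blinded.
- Primary outcome measures: percent change in weight and in BMI.
- Preliminary data from pilot study: among participants completing the programme, "the decreases were statistically significant in women, but not in men".
- Power calculation and sample size: the authors accept that intervention and ranch effects may be confounded and say that the analyses will account for this. They name no method.

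**The concern.** The plan calls these covariates important, leaves them out of the primary model, and makes even the sensitivity analysis discretionary with an open-ended list. The article makes this choice itself, so it is not merely a detail left to a fuller analysis plan.

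Three things are at stake.

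- **Balance.** Randomising about six ranches does not reliably balance the mix of workers. Because workers volunteer after their ranch's allocation is fixed, recruitment can also pull the arms apart. A random effect for ranch widens the standard error to allow for differences between ranches. It does not shift the estimate back when one arm happens to have more women.
- **Precision.** Differences between ranches that a measured covariate explains stay in the between-ranch variance, the component of the standard error that enrolling more workers per ranch cannot reduce.
- **Prespecification.** If adjusted and unadjusted results differ, nothing fixes which covariates are used or whether the adjusted result is produced at all.

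**Working it through.** **Inputs from the protocol article.** The design values are "To achieve 80% power with alpha level of 5% using two-sided, two-sample t-test", "mean difference of 4 and 3% with SD of 5"%, and "the average cluster (ranch) size in our study is 100". The minimum is six ranches. ICC values are those of Table 2: 0.01, 0.02 and 0.05.

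**Inputs that are assumptions.** The article gives neither the spread of gender mix between ranches nor any gender gap in percent weight change. I take SD 15 points for the share of women between ranches and a gap of 2 points, and vary both below.

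**Step 1: the plan's own figure.** A two-sample t-test with SD 5 needs 25.5 per arm for 4% and 44.6 per arm for 3%. Rounded up these are 26 and 45, which agrees with "the minimal total N required for detecting 4% difference is 52 (26 per group") and "that for detecting 3% difference is 90 (45 per group"). The inflation factors printed in Table 2 do not follow from a cluster size of 100 (for example 1 + 99 × 0.05 = 5.95, printed 10.95). That is a separate matter, and the calculation below does not use them.

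**Step 2: unadjusted power with six ranches.** Between-ranch variance is ICC × 25 and within-ranch variance is (1 − ICC) × 25. With three ranches of 100 per arm,

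SE = √[2 × (between + within/100) / 3], with power from the noncentral t on 4 df.

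At ICC 0.05: between 1.25, within 23.75, SE = √[2 × (1.25 + 0.2375)/3] = 0.996, and power for 3% is 62%.

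**Step 3: size of the gender imbalance.** The SD of the arm difference in share of women is 0.15 × √(2/3) = 0.122. Multiplied by a 2-point gap, the error in the treatment estimate has SD 0.24 points, a 95% range of about ±0.5.

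Allowing also for sampling 100 workers per ranch at 50% women, the SD of the arm difference is √[2 × (0.0225 + 0.0025)/3] = 0.129. The chance of an arm difference above 10 points is then 44%. For ranch SDs of 5, 10 and 20 points that chance is 8%, 27% and 55%. Across ranch SDs of 5 to 20 points and gaps of 1 to 3 points, the 95% range of the shift runs from about ±0.1 to ±1.0 points.

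**Step 4: power gained by removing it.** Gender contributes (0.15 × 2)² = 0.09 to the between-ranch variance. Subtracting 0.09, for a 3% difference:

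| ICC | Between-ranch variance | Share due to gender | SE before → after | Power before → after |
|---|---|---|---|---|
| 0.05 | 1.25 | 7% | 0.996 → 0.965 | 62% → 65% |
| 0.02 | 0.50 | 18% | 0.705 → 0.661 | 88% → 92% |
| 0.01 | 0.25 | 36% | 0.576 → 0.521 | 97% → 99% |

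**Step 5: baseline weight.** Suppose the arms differ by 2 kg at baseline and baseline and follow-up weight correlate at 0.90 to 0.97 (assumed, equal SDs). Raw follow-up weight would then be off by 2 × r = 1.8 to 1.94 kg, but change by only 2 × (1 − r) = 0.2 to 0.06 kg. Percent change may still depend on baseline level. With a baseline ICC of 0.01 to 0.05 and a correlation of 0.1 to 0.3 with percent change (assumed), the 95% range of the shift is 1.96 × correlation × 5 × √[2 × (ICC + (1 − ICC)/100)/3], or about ±0.1 to ±0.6 points.

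**The case against.** The strongest reply is that little is lost. The outcome is change from each worker's own baseline, ranches are matched in pairs, and chance imbalance between randomised ranches is sampling error that the ranch variance term is meant to carry. An SD of 0.24 points is small against a planned 3% to 4% and an SE of about 1.0 at ICC 0.05, where it makes up 0.09/1.4875 = 6% of the sampling variance. Most of this stands, and it limits the point to a modest gain. It does not justify leaving the adjustment optional. The change score and the matching do not directly address gender, and recruitment after allocation means that not all imbalance is chance.

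A reader might also infer more than the documents support:

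- **That the primary comparison has no protection against imbalance in baseline weight.** Step 5 shows that the change outcome removes most of it.
- **That these are the strongest predictors of weight change.** The article calls them important. It does not rank them and gives no correlations.
- **That the pilot shows women respond more than men.** Significance in one sex and not the other does not establish a difference in mean change. If real, it would suggest effect modification, which a main effect for gender does not test.
- **That adjustment would lift power for 3% at ICC 0.05 to between 74% and 83%.** Those values follow if the ICC falls to 0.035 or 0.025, that is, if covariates explain 30% to 50% of between-ranch variance. The gender assumptions used here explain 7% at that ICC. Nothing in the article supplies the rest.

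**Conclusion.** The point holds as a recommendation on prespecification and precision. The article leaves covariates it regards as important out of the primary model and makes their use discretionary, in a design with about three ranches per arm at the minimum and recruitment after allocation.

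Under the stated assumptions the imbalance error has SD about 0.24 points. Removing it gains about 3 percentage points of power for a 3% difference at ICC 0.05, about 3 at ICC 0.02 (88.2% to 91.6%) and about 2 at ICC 0.01. The gain would be larger only if baseline weight also explains between-ranch variance in percent change, which the article gives no means to judge. The figures assume exactly six ranches of 100, no credit for pair matching, and adjustment that removes the whole gender component.

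The shift would matter more if the true effect is well below the planned 3% to 4%; the article describes the pilot's reductions as small. The documents do not show that the primary result will be biased to a degree that could overturn a 3% to 4% effect.

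**What to change.** State in the Statistical analysis plan section that the primary model for percent change in weight and in BMI contains:

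- arm;
- ranch as a random effect;
- individual-level gender and baseline weight (or BMI) as fixed covariates.

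Report the model without covariates as the sensitivity analysis. Adjust each secondary outcome for its own baseline value. Replace the open-ended, optional wording with this fixed list, and use percent change throughout, since the analysis section refers only to change. State how degrees of freedom are obtained with so few ranches.

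The cost is a few sentences. Gender, weight, height and the clinical measures are already collected at baseline, and individual-level covariates take little from about 600 workers. The article reports follow-up as ongoing, so at that stage the change could still be made before analysis.

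This adjustment has two limits that should be stated with it. It does not test whether the effect differs by gender, and it does not cure selection on unmeasured factors from recruiting after allocation.
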